### Sample size estimation

2.3.

For Cohort 1, a total of 42 subjects will be randomized in a 2:1 ratio (28 in the trial arm: 14 in the control arm) to provide sufficient statistical power for determining the effectiveness of FMT in improving CARS scores compared to placebo. It is anticipated that, after 25 weeks of treatment, the mean reduction in CARS scores for the FMT group will be 5 points. Additionally, using a one-sided alpha level of 5 and 80% power, the proposed sample size will be able to detect the expected differences between the two groups. Considering a 15% dropout rate, the final sample size for Cohort 1 is expected to be 42 cases.

For Cohort 2, a sample size of 30 cases is considered sufficient to compare gut flora differences between children with ASD and healthy children.

### Randomization and blinding

2.4.

The Interactive Web Response System (IWRS) will be used to randomize subjects in Cohort 1. Prior to enrollment, a random coding table will be generated by non-blinded statisticians using the SAS 9.4 randomization process and imported into IWRS. The IWRS will be accessed by investigators using their respective codes, and eligible subjects will be assigned a unique drug number in IWRS and will receive the study drug corresponding to the drug number. Subjects who have been randomized, regardless of whether they are receiving study medication or not, cannot be reassigned to other subjects if the study is terminated for any reason.

Cohort 1 will be performed in a double-blind manner. From the time of randomization, their treatment will be blinded, as well as the investigator, study team and anyone involved in the trial until the database is locked. The study drugs will also be blinded by non-blinded personnel not involved in this study, according to a drug randomization coding list provided by non-blinded statisticians. The computer program generating the randomization codes and the randomization code sheet will be used as a blinded base and kept securely by the unblinded team. The blinding will be kept strictly confidential until the final blinding, except in the circumstances such as emergency unblinding or suspected unexpected serious adverse reactions, in which case individual blinding may be performed by designated project personnel. Blinding personnel involved in the execution of the trial will not be informed of any of the subject’s blinding status until final blinding is completed, except in cases of emergency blinding.

### Interventions

2.5.

#### Test drug

2.5.1.

The drug in this study will be XBI-061, and the placebo will be XBI-061 placebo, both having the same appearance, smell, weight and available in two sizes: 6 mL/bottle and 0.6 mL/bottle, containing 1 × 10^10^ to 1 × 10^11^ live bacteria and 1 × 10^9^ to 1 × 10^10^ bacteria, respectively. The ASD children in the placebo group will receive the same dose every time as the treatment group. One bottle of the bacterial liquid or placebo will correspond to approximately 70 mL of the therapeutic drink. Based on the volume the child can tolerate, the bacterial liquid or placebo will be removed from the cold refrigerator, dissolved in a therapeutic drink, shaken well, and immediately consumed.

#### Experimental flow

2.5.2.

##### Cohort 1

2.5.2.1.

The study flow for Cohort 1 will be divided into seven phases: screening period, bowel preparation, first treatment dose, intensive treatment, maintenance treatment, follow-up, and exit (Figure 2). The patients will undergo stool and urine sample collection, relevant examinations, and scale assessments (Table 1). During the screening period (D-21 ~ D-7), the eligible ASD patients will be assessed based on the implemented scales and complete all required examinations, and the baseline data will be recorded. In the bowel preparation phase (D-6 ~ D-1), patients in both the trial and control groups will undergo bowel preparation with oral rifaximin suspension or rifaximin mimetic for five days at 0.1 g each time, four times daily, followed by one day of polyethylene glycol bowel cleansing. The first treatment dose (D1 ~ D7) will involve administering a total of approximately 700 mL of the therapeutic drink (containing 66 mL of bacterial liquid or placebo) orally over 3 to 5 consecutive days of the week, depending on the subject’s acceptance of the therapeutic drink and the volume available for each dose. Intensive treatment (D8 ~ D28) will involve an intensive dose of approximately 60 mL of the treatment drink (containing 6 mL of bacterial fluid or placebo) once a week for 3 weeks. During the maintenance treatment phase (D29 ~ D84), once weekly doses of approximately 10 mL of the treatment drink (containing 0.6 mL of bacterial liquid or placebo) will be administered for 8 weeks. During the follow-up period (D85 ~ D169), the subjects will receive the same rehabilitation as during the treatment period. They will be discharged at week 25 after completion of the end-visit examination (D170). Throughout the treatment period, they will be asked to adhere to the “Dietary Manual for People with Autism Receiving FMT Therapy” as closely as possible, with a legal guardian completing a weekly dietary record form.

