### Study design

2.1.

This is a single-center, double-blind, double-modeled, randomized, interventional clinical study aiming at exploring the efficacy and safety of FMT formulation on an interventional treatment of children with ASD. The degree of improvement in their symptoms will be assessed using several scales. Additionally, changes in the composition and structure of their intestinal flora and metabolites of the flora in their blood, urine and feces before and after treatment will also be assessed by macro-genomic sequencing and metabolomics. The study will also evaluate the differences in the gut flora of children with ASD and healthy children and the acceptability of FMT pediatric preparations by children with ASD and their legal guardians.

The primary endpoint of the study is the change from baseline in Childhood Autism Rating Scale (CARS) scores in children with ASD after 12 and 24 weeks of treatment. The secondary endpoints are the variations in assessment scales, and gut flora and included five main points:

(1) Variations in scores from baseline in the Social Responsiveness Scale (SRS), Autism Behavior Checklist (ABC), Psychoeducational Profile Third Edition (PEP3), Gastrointestinal Symptom Rating Scale (GSRS), and Children’s Sleep Habits Questionnaire (CSHQ) after 12 and 24 weeks of treatment;(2) Variations in gut flora characteristics (including alpha-diversity, flora composition, beta-diversity, colonizing bacteria, differential bacteria, and metabolic pathway function) in children with ASD after treatment compared to baseline and donors;(3) Differences in intestinal flora characteristics (including alpha-diversity, flora composition, beta-diversity, differential bacteria, and metabolic pathway function) between children with ASD (baseline) and healthy children;(4) The incidence of adverse events during the treatment of children with ASD;(5) Variations in the FMT acceptance scale scores for participants with ASD and their legal guardians.

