The patients will be divided into two cohorts: Cohort 1 will include 42 children aged 3–9 years diagnosed with ASD, while Cohort 2 will include 30 healthy children aged 3–9 years. The sex ratio and age range of children enrolled in Cohort 1 and Cohort 2 will be kept roughly the same. In Cohort 1, subjects who meet the entry criteria will undergo a two-week screening visit after the legal guardian signs the informed consent. They will then be randomly allocated to either the trial or control group in a 2:1 ratio. Children in the trial group will undergo rehabilitation and FMT, while the control group will receive rehabilitation and placebo. All children will undergo a 12-week treatment period following the completion of bowel preparation and followed up for 12 weeks, during which they will receive only rehabilitation. A homogenous rehabilitation scheme will be performed on all the ASD children in Cohort 1. The study participants will be discharged at week 25 after the end visit. In Cohort 2, after the legal guardian signs the informed consent, they will undergo a physical examination, assessment of vital signs, and various laboratory examinations within two weeks to confirm their health status. Blood, urine, and fecal samples will be collected within one week, and the children will be discharged. Metabolomics analysis will be performed on blood and urine samples, while macro-genomic sequencing and metabolomics analysis will be conducted on fecal samples.

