(1) Use of probiotics, antibiotics, antifungal, prebiotic and other drugs affecting the intestinal microflora in a planned way within the last 3 months or in the following 6 months.(2) Diagnosis of intestinal obstruction (including partial obstruction), or severe ulcerative damage to the bowel;(3) Diagnosis of an immunodeficiency disorder or autoimmune disease, including but not limited to rheumatoid arthritis, systemic lupus erythematosus, ankylosing spondylitis, desiccation syndrome, Hashimoto’s thyroiditis, toxic diffuse goiter, autoimmune hemolytic anemia, idiopathic thrombocytopenic purpura, Crohn’s disease, psoriasis, glomerulonephritis, nephrotic syndrome;(4) A previous history of severe food or drug allergy;(5) A history of severe fever and/or severe infection within 7 days prior to enrolment;(6) Renal insufficiency and hepatic dysfunction, for instance, alanine aminotransferase level > 1.5 times the normal upper limits, aspartate aminotransferase level > 1.5 times the normal upper limits, or serum creatinine level > 1.5 times the normal upper limits;(7) Be in an immunosuppressed state (i.e., presence of a neoplastic disease or organ transplantation) underwent or undergoing chemotherapy;(8) Diagnosed with inflammatory bowel disease, celiac disease, irritable bowel syndrome or eosinophilia, oesophagitis, eosinophilic gastroenteritis or similar conditions;(9) Diagnosis of blindness, deafness, cerebral palsy, etc.;(10) Participation in another clinical study or an interventional clinical study with non-conventional rehabilitation within 4 weeks prior to enrolment;(11) A previous history of HIV, hepatitis B virus, hepatitis C virus or syphilis infection, or a parent with HIV infection;(12) A treatment of intra-abdominal surgery (excluding appendectomy or cholecystectomy) within the past 60 days prior to screening and/or planned invasive surgery/hospitalization during the study period;(13) Presence of certain prominent symptoms, including but not limited to stereotyped repetition, aggression, self-injury, vandalism, severe emotional behavioral problems and extreme hyperactivity, and requiring pharmacological treatment as per the principal investigator assessment;(14) Poor compliance (i.e., therapeutic drinks taken at less than 80%), using the following formulas to estimate:

Dose = total dose - remaining dose;Adherence rate (a quantitative indicator of adherence) = (dose taken/total amount) x 100%.

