Although FMT has been shown to effectively improve the symptoms of ASD, there is still no consensus on the optimal dose and treatment regimen for FMT in ASD patients (De Angelis et al., 2015). Chen et al. used an individualized daily intake of fecal bacteria (Chen et al., 2022). Our study will use standard bacterial fluids administered in three phases: first-dose treatment, intensive treatment, and maintenance treatment. Prior to treatment, antibiotics were used to clean the bowel, making this the first study to use bacterial fluids in three phases of treatment, which has significant implications for the further development of clinical applications of FMT. The critical period after antibiotic use was likely the most favorable for colonizing the gut by foreign bacteria (Kang et al., 2019). Therefore, our study’s first week of treatment will involve a high bacterial dose, followed by three weeks of intensive treatment and eight weeks of maintenance treatment. The bacterial liquid in this study will be dissolved in drinks, making it easier for children with ASD to swallow, which will increase the acceptability of FMT treatment. This study hypothesizes that FMT will target specific ASD symptoms, gastrointestinal symptoms and sleep symptoms, and aim to identify the bacteria and metabolites associated with improved symptoms. This study is a double-blind randomized controlled trial, but some limitations still exist. Firstly, the sample size might be small, with only 42 patients enrolled in this study. Further expansion of sample size will need to demonstrate the efficacy of fecal microbiota transplantation fluid for autism. Secondly, future trials will group children with ASD according to different core symptoms to explore the precise targeting of FMT treatment for ASD symptoms and compare the effects of FMT treatment within and between groups. Thirdly, a longer follow-up time will enable better observation of the duration of improvement in ASD symptoms and the safety and efficacy of FMT. This study will have only one follow-up and willnot track the long-term impact of FMT on children with ASD. Fourthly, besides diet, probiotics and other factors, there are many factors affecting gut microbiota. This study will not fully consider the mixed factors affecting gut microbiota, such as living habits, age, etc.

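### The bowel preparation is rifaximin or a rifaximin mimetic with no arm named; if it differs by arm, the trial compares whole regimens, and the CARS difference cannot be credited to FMT alone

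*Protocol article*

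**What the plan says.** Section 2.5.2.1 (Experimental flow, Cohort 1) describes the days before treatment as follows: "patients in both the trial and control groups will undergo bowel preparation with oral rifaximin suspension or rifaximin mimetic". Five days of this are followed by one day of polyethylene glycol. The section does not say who receives rifaximin and who receives the mimetic. Sections 2.4 and 2.5.1 do not settle it either: they deal with coding of the study drug and with XBI-061 and its placebo.

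Other places bear on the same point:

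- Section 2.1, design label: "This is a single-center, double-blind, double-modeled, randomized, interventional clinical study".
- Section 2.1, what the arms receive: "Children in the trial group will undergo rehabilitation and FMT, while the control group will receive rehabilitation and placebo".
- Section 2.3, purpose of the comparison: "for determining the effectiveness of FMT in improving CARS scores compared to placebo". The main objective at the end of the Introduction is likewise worded as the effectiveness of FMT.
- Section 5 (Discussion): "Prior to treatment, antibiotics were used to clean the bowel". Neither an arm nor the mimetic is mentioned.
- Section 5, on why the antibiotic is there: "The critical period after antibiotic use was likely the most favorable for colonizing the gut by foreign bacteria".
- Section 2.2, exclusion criterion 1, groups antibiotics with agents that alter the flora: "Use of probiotics, antibiotics, antifungal, prebiotic and other drugs affecting the intestinal microflora".
- Section 2.5.2.1, baseline: "During the screening period (D-21 ~ D-7), the eligible ASD patients will be assessed based on the implemented scales". Bowel preparation follows at D-6 to D-1.

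**The concern.** A dummy rifaximin has a purpose only if some children do not get the real one. The article names two components that could be blinded with a dummy: the bacterial liquid with its placebo, and rifaximin with its mimetic. If the mimetic goes to the control arm, the randomized contrast is rifaximin preparation plus FMT against mimetic plus placebo. The objective and the sample-size section name only the second component of each pair.

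At stake is the primary conclusion. A CARS difference between arms would be reported as an effect of FMT when part of it could come from the antibiotic, or from the antibiotic and FMT acting together. The aims on flora change before and after FMT and on the safety of the FMT formulation carry the same ambiguity, as does the exploratory metabolomic aim.

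**Working it through.** **1. What each possible allocation would imply**

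- *Rifaximin with FMT, mimetic with placebo.* The wording in Section 2.1 and Section 2.3 is incomplete, because the arms differ by two components. The Discussion sentence on antibiotics would then describe the active arm only.
- *Rifaximin for every child.* The contrast is FMT versus placebo as worded, but the mimetic in Section 2.5.2.1 has no evident role.
- *Some other rule.* That rule is not stated in the text.

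Under each reading at least one place needs correction or completion.

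**2. What the contrast estimates under the first reading**

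Write Y(p, t) for the mean CARS change with preparation p and treatment t. The between-arm difference is

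Y(rif, FMT) − Y(mim, plac) = [Y(rif, FMT) − Y(rif, plac)] + [Y(rif, plac) − Y(mim, plac)].

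The first bracket is the effect of FMT after rifaximin preparation. The second is the effect of rifaximin alone. No child would be observed under (rif, plac), so the brackets cannot be estimated separately. Rifaximin exposure equals allocation for all 42 children (28 exposed, 14 not). The two indicators are identical, and neither covariate adjustment nor a larger sample separates them.

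**3. Whether any measurement isolates the preparation**

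The primary endpoint is change in CARS from baseline to 12 and 24 weeks. Baseline is D-21 to D-7, preparation is D-6 to D-1, and dosing starts on D1. Table 1 schedules no scale and no stool sample in the bowel-preparation column, and its footnote starts fortnightly stool sampling only after treatment begins. Every change from baseline therefore includes whatever the preparation did.

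**4. Illustration of size (assumptions, not plan figures)**

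The planned total of 42 cannot be reproduced forwards: Section 2.3 gives a 5-point mean reduction in the FMT group, 80% power, a one-sided alpha of 5 (read as 5%) and 15% dropout, but no SD and no placebo change. Assume a 5-point between-arm difference and 36 evaluable children split 24:12. As a check, 36 × 1.15 = 41.4, rounded up to 42, and 36 / 0.85 = 42.4, rounded up to 43. Solving back:

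- SD = 5 / [(1.645 + 0.842) × √(1/12 + 1/24)] = 5 / (2.487 × 0.3536) = 5.69.
- Standard error of the difference = 5.69 × 0.3536 = 2.01.

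Suppose FMT does nothing and rifaximin alone shifts CARS by r points. The chance of a significant result credited to FMT is Φ(r / 2.01 − 1.645):

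| r (points) | Probability |
|---|---|
| 0 | 5% |
| 1 | 13% |
| 2 | 26% |
| 3 | 44% |

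Suppose instead that the 5-point total is r from rifaximin and 5 − r from FMT. Power for the FMT part alone would be Φ((5 − r) / 2.01 − 1.645), that is 80%, 64%, 44% and 26% for r = 0, 1, 2 and 3. The documents give no rifaximin effect on CARS, so the range 0 to 3 is assumed. The point does not depend on it.

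**The case against.** The strongest reply has four parts.

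- *The passages do not strictly contradict one another.* A reader might infer that Section 2.1 says the arms differ solely in FMT, and that the Discussion says every child had an antibiotic. Neither statement is there. Section 2.1 lists what each group receives without excluding other differences, and the Discussion sentence sits in an account of the active regimen. With matched dummies for both components, all these places can be read together. This stands: the defect is an unstated allocation combined with attribution wording that does not allow for it, and not a proven contradiction.
- *The allocation is inferred.* Reading double-modeled as double-dummy is an interpretation. Figures 1 and 2 were not available in the text reviewed, and the full protocol may name each arm's preparation. This stands too, and it is why the confounding is put conditionally. It does not remove the point, because the article does describe the preparation and, separately, fixes the conclusion as one about FMT.
- *A whole-regimen comparison is a legitimate design.* Agreed. The Discussion presents antibiotic preparation as part of the strategy, and a randomized comparison of full regimen with full dummy regimen is valid for the regimen. The objection here is to the label.
- *The consequence can be overstated.* A reader might infer that no flora finding could then be credited to FMT. That goes too far: secondary endpoint 2 includes colonizing bacteria and comparison with donors, and donor-strain colonization is specific to the transplant. Likewise, the article's statements about antibiotics concern the flora. They do not show that a five-day course moves CARS at 12 or 24 weeks.

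Polyethylene glycol is described for both groups and adds no imbalance.

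**Conclusion.** The point holds in conditional form. The text leaves open which arm receives rifaximin, the most natural reading pairs it with FMT, and on that reading the plan leads to a conclusion about FMT alone that the design cannot support. Confounding of the two components would then be complete (28 versus 14) for CARS and for general flora and metabolite differences, with donor-strain colonization excepted.

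How much of any CARS difference would be misattributed is unknown. The illustrative 13% to 44% chance of a significant result wrongly credited to FMT rests on an assumed rifaximin effect of 1 to 3 points, an assumed 5-point between-arm difference and a back-solved SD. If every child receives the same preparation, there is no confounding and only the mimetic wording is wrong. Confidence is moderate, because it turns on an allocation that the text does not give. The point deserves correction but does not invalidate the design.

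**What to change.** Reconcile Section 2.1, Section 2.3, Section 2.5.2.1 and the Discussion, and state in one sentence which preparation each arm receives.

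- If preparation differs by arm, word the comparison, the primary objective and the permitted conclusion as the whole regimen (rifaximin preparation plus FMT versus mimetic plus placebo). State that differences in CARS, and general differences in flora and metabolites, will not be attributed to FMT alone; donor-strain colonization may still be credited to the transplant.
- If preparation does not differ, correct the mimetic wording in Section 2.5.2.1.

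No preparation regimen is recommended here; that choice is clinical. The cost is wording only, with no change to sample size, visits or analysis. The downside, if the arms differ, is that the claim narrows from FMT to the FMT regimen.

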This is a double-blind randomized controlled trial aimed at assessing the effectiveness of FMT in improving symptoms of ASD (Figure 1). The main objective of this study is to evaluate the effectiveness of the FMT technique in improving symptoms in children with ASD and to identify the core symptoms of ASD that can be improved by FMT. Additionally, there are four secondary aims: (1) to compare changes in the composition of gut flora in children with ASD before and after FMT, (2) to compare differences in gut flora between children with ASD and healthy children, (3) to assess the safety of the FMT pediatric formulation in children with ASD, and (4) to evaluate the acceptability of the FMT pediatric formulation to children with ASD and their legal guardians. The exploratory aim of the study is to identify changes in the metabolomics of children with ASD before and after receiving FMT.

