**Figure 2 fig2:**
[figure not shown]
Overall process of the clinical trial.

**Table 1 tab1:** Inspection schedule for cohort 1.

Parameters	Baseline	Bowel preparation	Treatment period						Follow-up
			First dose treatment	Intensive treatment	Maintenance treatment				
Time window	D-21 ~ D-7	D-6 ~ D-1	D1 ~ D7	D8 ~ D28	D29 ~ D42	D43 ~ D56	D57 ~ D71	D71 ~ D84	D85 ~ D169
Informed consent	X								
Inclusion and exclusion criteria	X								
Demographic data^a^	X								
Medical and treatment history	X								
Height	X								
Weight	X							X	X
Vital signs^b^	X							X	X
Allergy history	X								
Health checkup	X							X	X
Routine blood test	X							X	X
Blood biochemistry	X							X	X
Urinalysis	X							X	X
Fecal routine	X							X	X
Fecal sample collection^c^	X			X		X		X	X
Urine sample collection^c^	X			X		X		X	X
Blood sample collection^c^	X							X	X
Bowel preparation		X							
FMT			X						
CARS	X			X		X		X	X
SRS	X			X		X		X	X
GSRS	X			X		X		X	X
ABC	X			X		X		X	X
CSHQ	X			X		X		X	X
PEP3	X			X		X		X	X
rehabilitation training	X								
Acceptance survey^d^			X	X				X	
Diet Record	X								
Adverse event record	X								
Combined medication record	X								

FMT, Fecal Microbiota Transplantation; CARS, Childhood Autism Rating Scale; GSRS, Gastrointestinal Symptom Rating Scale; ABC, Autism Behavior Checklist; PEP3, Psychoeducational Profile(Third Edition); SRS, Social Responsiveness Scale; CSHQ, Children’s Sleep Habits Questionnaire.

1 Demographics: date of birth, age, sex, ethnicity.

2 Vital signs: temperature, blood pressure, heart rate (pulse), respiratory rate.

3 Sample collection:

a Stool sample collection: Stool samples will be collected for macro-genome sequencing and metabolomic analysis during the screening period, every fortnight after the start of treatment for macro-genome sequencing, and every four weeks for metabolomic analysis until the end of the study.

b Urine sample collection: Urine samples will be collected for metabolomic analysis during the screening period and every four weeks from the start of treatment until the end of the study.

c Blood sample collection: Blood samples will be collected for metabolomic analysis during the screening period, at the end of treatment (week 13), and at the end of the study (week 25) for metabolomic analysis and safety data collection in the blood.

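### Flora and metabolite aims worded as before-after change cannot credit FMT alone, because the dietary manual and bowel preparation come in after the baseline samples; they should be defined against placebo

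*Protocol article*

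**What the plan says.** **Diet.** Section 2.5.2.1 (Cohort 1): "Throughout the treatment period, they will be asked to adhere to the" dietary manual as closely as possible, "with a legal guardian completing a weekly dietary record form". The sentence covers Cohort 1 and singles out no arm.

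**Treatment window.** Section 2.1: "All children will undergo a 12-week treatment period following the completion of bowel preparation". Table 1 heads this period D1 to D84. Follow-up is described in Section 2.1 as "followed up for 12 weeks, during which they will receive only rehabilitation".

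**Baseline.** Section 2.5.2.1: "During the screening period (D-21 ~ D-7), the eligible ASD patients will be assessed based on the implemented scales". The Table 1 footnote on stool reads: "Stool samples will be collected for macro-genome sequencing and metabolomic analysis during the screening period, every fortnight after the start of treatment". Screening urine and blood are handled in the same way. Bowel preparation (rifaximin or its mimetic, then polyethylene glycol) follows at D-6 to D-1.

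**Aims and endpoints.** Secondary aim 1 in the Introduction is "to compare changes in the composition of gut flora in children with ASD before and after FMT". The exploratory aim is the same kind of comparison for metabolomics. Secondary endpoint 2 in Section 2.1 compares post-treatment flora with baseline and with donors. The Abstract sets the FMT group, before and after treatment, against the 30 healthy children. None of the four names placebo as comparator.

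**Diet as an influence.** The Discussion accepts that "besides diet, probiotics and other factors, there are many factors affecting gut microbiota".

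**The concern.** A before-after comparison credits the treatment with everything that changes between the two samples. Here the diet guidance and FMT start together in every FMT-arm child, with bowel preparation just before. The article itself lists diet among the influences on gut flora.

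Three kinds of result are at stake:

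- **Flora or metabolite change.** A shift between baseline and week 12 that is partly due to diet or bowel preparation could be reported as the effect of FMT.
- **Movement towards healthy children.** Cohort 2 is sampled once, and no diet instruction is described for it. If FMT-arm children come to resemble Cohort 2 more closely, the before-after comparison cannot say why.
- **Markers.** The Introduction looks for bacterial and metabolic markers by correlating changes in symptom scales with flora and metabolites. A shift caused by a co-intervention can enter that search.

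**Working it through.** No stated sample size, power or alpha figure bears on this point, so there is no plan figure to reproduce. The check sets the windows side by side and splits the change from baseline into its parts.

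**Step 1: windows (Section 2.5.2.1 and Table 1)**

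- Baseline samples: D-21 to D-7
- Bowel preparation: D-6 to D-1
- Treatment period, for which the manual is stated to apply: D1 to D84 (84 / 7 = 12 weeks, matching Section 2.1)
- Follow-up: D85 to D169; diet not mentioned

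**Step 2: samples against the diet window.** Table 1 marks stool collection in five columns. Three lie inside D1 to D84 (D8-D28, D43-D56, D71-D84). Baseline lies before the window. Follow-up (D85-D169) lies after it. Every on-treatment column is therefore under diet guidance and the baseline column is not. Bowel preparation separates baseline from all later samples.

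**Step 3: change from baseline during treatment.** Let F be the effect of FMT, D of diet guidance, B of bowel preparation and T of time, including rehabilitation.

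- FMT arm (n = 28): change = F + D(FMT) + B(FMT) + T
- Placebo arm (n = 14): change = D(placebo) + B(placebo) + T

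The first line alone cannot be solved for F. That line is what the two aims, endpoint 2 and the Abstract's comparison describe. Adding donors or healthy children as a reference does not help, because neither group passes through the same D, B and T.

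**Step 4: the randomised contrast**

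- Difference = F + [D(FMT) - D(placebo)] + [B(FMT) - B(placebo)]

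T cancels. D cancels if both arms follow the manual to a similar degree, which blinding makes reasonable. B cancels if both arms receive the same preparation. The article says the two groups receive rifaximin or a mimetic without tying either to an arm. If they differ, the contrast estimates the effect of the whole assigned regimen, which is still a clear randomised quantity.

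**Step 5: similarity to healthy children.** Let d(t) be a child's distance at time t from the Cohort 2 centroid. The quantity free of the shared terms is the mean of d(12) - d(0) in the FMT arm minus the same mean in the placebo arm. The centroid is the same for both arms.

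**The case against.** The strongest reply is that the control already exists and the article intends to use it. Section 2.6 names Mann-Whitney U and Kruskal-Wallis tests for flora and metabolites between groups and names no paired test. The Figure 1 caption speaks of comparing three groups. Which contrast is inferential is also a detail that a condensed article may leave to the analysis plan.

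Part of this stands: between-group work is foreseen, so the remedy is mostly a matter of definition. But neither place says that the comparison is of change from baseline by arm, and the groups in Section 2.6 may include the healthy children. The aims and endpoint 2 are stated in the article, and as stated they are before-after comparisons.

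Three stronger readings are tempting, and the documents do not support them.

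- **That the diet stops at D84.** A reader might infer this from the stated window and from the rehabilitation-only follow-up. No sentence says so, and the latter may only contrast follow-up with the study product. The diet record row of Table 1 shows a mark under Baseline only, but so do rehabilitation and adverse event recording, which clearly continue. It may be a merged cell, and the extracted text cannot settle it.
- **That diet changes at both ends, so that a week-24 reversal could be mistaken for lost engraftment.** This depends on the unproven stop. Even if the diet did stop, baseline and week 24 would both be off the manual, with only carry-over between them.
- **That the overstatement of FMT can be given as a factor.** The article gives no diet share and does not show the manual. It is not known whether the manual alters any child's intake. A scalar factor also ignores bowel preparation and suits beta-diversity poorly.

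**Conclusion.** The point holds for the before-after wording. A change during treatment within the FMT arm cannot be attributed to FMT alone, because diet guidance and bowel preparation both come between the baseline and on-treatment samples. The overlap in timing is complete by design: it covers all 28 FMT-arm children and all three on-treatment stool columns. It reaches four statements: secondary aim 1, the exploratory aim, secondary endpoint 2 and the Abstract's healthy-child comparison. The size of the resulting error is unknown and is not estimated here.

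The primary CARS contrast with placebo is not affected, and the randomised flora and metabolite contrast is protected from the shared diet term. This rests on two assumptions: that the manual is given to both arms, as the undivided wording of Section 2.5.2.1 implies, and that adherence is similar in the two blinded arms.

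**What to change.** 1. Define secondary aim 1, the exploratory metabolomics aim and secondary endpoint 2 as the FMT-versus-placebo difference in change from baseline.
2. For similarity to healthy children, use the change in distance to the Cohort 2 centroid, compared between arms. Donor similarity can be treated in the same way.
3. Label within-arm changes, including FMT-arm change against donors or healthy children, as descriptive.
4. State whether the diet instruction and the weekly diet record apply before D1 and after D84, and compare recorded adherence between arms to check the cancellation assumption.
5. State which bowel preparation each arm receives, so that readers know whether the contrast isolates FMT or describes the whole regimen.

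The cost is wording and analysis definition. The samples are already scheduled in both arms, and nothing changes for families. The price is precision: a contrast of 28 against 14 children is noisier than a within-arm change, which is a reason to report both with their proper labels.
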